### Recruitment and screening

2.6

In the Frisius Medical Center Leeuwarden, the routine medical care for patients suspected of having sleep apnea is as follows: patients are referred to the Multidisciplinary Sleep Centre (MDSC) by the pulmonologist, ENT surgeon, neurologist or general practitioner. All patients are discussed during the MDSC meeting after the diagnostic work-up. The diagnostic evaluation of OSA consists of multiple tests performed according to the national OSA guidelines [14]. These include completing questionnaires like the Holland Sleep Disorders Questionnaire (HSDQ) [25], ESS [23] and undergoing a PG. Depending on the results of the PG, patients may be referred to the neurologist, to the pulmonologist or ENT surgeon. In cases of suspected obstructive sleep apnea, patients are referred to the ENT surgeon for further evaluation, including physical examination and DISE. Patients demonstrating concentric collapse or no collapse of relevant anatomical structures (velum, oropharynx, tongue base or epiglottis) are considered ineligible for surgery. The findings of the examination are discussed with the patient and together with the physician a treatment plan is made that may consist of surgery via TORS (if DISE results permit), CPAP or MAD. If the patient chooses CPAP, referral to pulmonologist is indicated and if MAD is chosen, referral to maxillofacial oral surgeon is indicated. If the patient chooses surgical treatment, patient will be scheduled for surgery. After discussion of the DISE findings and available treatment options, patients iwho are eligible for both treatment arms will be informed about the clinical trial. If the patient is interested, the investigator will contact the patient for further explanation of the study.

After inclusion and randomization, group 1 will undergo TORS and will be hospitalized post-surgery, which is expected to be 3 days. Patient will be discharged home with pain medication and will visit the outpatient clinic after 6 weeks for evaluation of surgical wounds. Group 2 will be assessed by either a pulmonologist or a MFO surgeon. They will have an evaluation of treatment after 3 months. Time point 0 (T0) starts when patient undergoes surgery and the first day of usage of CPAP or MAD. The TORS group will complete questionnaires at 3, 6 and 12 months and will undergo PG at 6 and 12 months for evaluation of the treatment. Then, they will also have evaluation of swallowing quality of the speech language pathologist at baseline, 2 days after surgery (while hospitalized) and 6 weeks. The CPAP or MAD group will have outpatient follow-ups at the pulmonologist or MFO surgeon at the same time points. Then, they will also complete the questionnaires (3,6 and 12 months) and will undergo PG at 6 and 12 months. The CPAP will be read out at 3,6, and 12 months. For the TORS group, in addition to standards PG and quality of life questionnaires, pain scores using VAS will be recorded. The length of hospital stay will also be monitored.

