## Introduction

1

In obstructive sleep apnea (OSA) syndrome, repetitive partial or complete collapse of the upper airway during sleep leads to nocturnal hypoxia and interruption leading to daytime sleepiness [1]. OSA is associated with an increased risk of comorbidities such as hypertension, type 2 diabetes mellitus, and cardiovascular disease [2,3]. The gold standard treatment for OSA is continuous positive airway pressure (CPAP). CPAP effectively reduces apnea hypopnea index (AHI), improves sleep quality and decreases cardiovascular co-morbidities [4,5]. Regardless of the benefits, 30% of patients refuse treatment with CPAP due to several reasons including pressure effect of the mask [4] [[5], [6], [7]]. Another challenge of CPAP is treatment adherence, which requires a minimum usage of 4 h per night on at least 70% of nights. A study by Koehler et al. has shown that after 3 months adherence rates were 54% [8]. Mandibular advancement devices (MADs) are another non-surgical treatment modality that effectively reduce AHI [9], though they are less effective than CPAP. However, MADs demonstrate higher treatment adherence compared to CPAP [10].

For OSA patients who are unable to tolerate CPAP or MADs and are eligible for surgery, transoral robotic surgery (TORS) has emerged as an effective treatment option. TORS focuses on the obstruction at BOT, permanently enlarging the upper airway by removing lingual tonsil tissue. However, like all surgeries, TORS carries inherent risks such as postoperative bleeding, stenosis, infection and dysphagia, all risks that non-surgical therapies do not present. While studies have shown that TORS effectively reduces AHI [11,12], randomized trials comparing its efficacy to standard non-surgical therapies are lacking.

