In this proposed study, a trial designed to address a clinically pragmatic question: whether TORS, an accepted surgical treatment for selected patients but typically positioned after non-surgical therapies in the routine care pathway, provides outcomes that are equal or superior to standard non-surgical management. In this parallel-group, randomized controlled trial with a 1:1 allocation ratio, we will compare TORS to non-surgical therapy (CPAP or MADs). Following a superiority framework, it aims to determine whether TORS provides better sleep outcomes, long-term efficacy, and quality of life while assessing complications, compliance, and functional outcomes. These comparators were chosen because CPAP and MADs are well-established, non-invasive treatments recommended in clinical guidelines and are typically chosen as first options in routine care. Historically, surgery has been considered a last resort in the management of OSA. Therefore, CPAP and MAD are pooled as non-surgical therapy in this trial to reflect real-world conventional management rather than to compare TORS against a single treatment modality. The primary objective of this study is to quantify the effectiveness of TORS relative to CPAP or MADs in treating OSA. Additionally, this study aims to determine the long-term outcomes of TORS compared to conventional therapy, assess functional sleep outcomes in patients undergoing TORS. Furthermore, it will evaluate health-related quality of life in both treatment groups and examine patient compliance with non-surgical therapy. By addressing these objectives, this study aims to provide comprehensive insight into the role of TORS as a treatment modality for OSA, helping to inform clinical decision-making and improve patient outcomes.

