### Study outcomes

2.5

The primary endpoint of this study is the mean AHI measured 6 months post-intervention. This time point was selected because it reflects the earliest clinically relevant assessment at which treatment effects are expected to be stable in both arms: after postoperative recovery following TORS and after establishment of CPAP/MAD use and adherence. The PG will be performed at baseline, 6 months and 12 months. A lower AHI reflects improved airway patency and is thus clinically meaningful in assessing treatment effectiveness between groups. Twelve month follow up is included as an important secondary endpoint to evaluate durability of treatment effects in this chronic condition. Secondary outcomes include: (1) 50% reduction of AHI at 6 months compared to baseline and or AHI below 20/h (Sher's criteria) [2,21] reduction of AHI at 12 months to <5/h will be defined as surgical cure [3,22] differences in mean ODI 4% values at 6 months and 12 months, and reduction of ODI 4% to 25% relative to baseline will be defined as clinically relevant [4,22] differences between FOSQ-35 [15] scores at 3 months, 6 months and 12 months in which an increase of 10% of the score compared to baseline on the FOSQ-35 questionnaire will be defined as clinically relevant [5,22] differences between scores of ESS at 3 months, 6 months and 12 months and a reduction on the ESS to <10 will be defined as clinically relevant [6,23] differences between scores of quality of life questionnaires EQ-5D-5L [19] at 3 months, 6 months and 12 months [7]; differences in scores on the visual analogue scales (VAS) for snoring, tiredness and globus in all patients between baseline, 3, 6 and 12 months [8]; VAS scores swallowing and taste for patients in the TORS group at baseline compared to 3 months, 6 months and 12 months.

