Other study parameters will be descriptive parameters such as age, gender, body mass index, history of smoking, reflux complaints, dentition, history of medication use including sleep medication, physical examination (Friedman score of the tongue tonsils and throat tonsils), measurements of DISE such as tongue base collapse classified by velum oropharynx tongue base epiglottis classification system (VOTE) [24]. Other PSG measurements are also included as study parameters such as ODI 4%, lowest desaturation (LSAT), desaturations below 90%, number of hypopneas, number of apneas and snoring time. For CPAP and MAD compliance will be assessed by pulmonologists and maxilla oral facial surgeons including follow up time, start date of treatment. Quality of life assessments and swallowing quality through MDADI [18] and SWAL-QoL [20] at baseline 3 months, 6 months and 12 months for the TORS group.

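### Follow-up is timed from surgery or first device use, so a randomised patient in either arm who never starts has no due date for the primary polygraphy, and the AHI comparison describes starters only

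*Protocol article*

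**What the plan says.** **Clock.** Section 2.6 (Recruitment and screening) defines the origin: "Time point 0 (T0) starts when patient undergoes surgery and the first day of usage of CPAP or MAD". The same section places questionnaires at 3, 6 and 12 months and PG at 6 and 12 months. For controls it adds "The CPAP or MAD group will have outpatient follow-ups at the pulmonologist or MFO surgeon at the same time points" and "The CPAP will be read out at 3,6, and 12 months".

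**Primary endpoint.** Section 2.5 (Study outcomes): "The primary endpoint of this study is the mean AHI measured 6 months post-intervention".

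**Compliance.** One aim in the Introduction is to "examine patient compliance with non-surgical therapy". Section 2.5 says how: "For CPAP and MAD compliance will be assessed by pulmonologists and maxilla oral facial surgeons including follow up time, start date of treatment". Section 2.10 (Statistical analysis) reports adherence descriptively. None of these states a denominator.

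**Analysis set.** Section 2.10 says that the full analysis set follows intention to treat. It then leaves out patients with major protocol violations, without post-baseline data, or without the study intervention. Missing values are not imputed.

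**Background.** The Introduction reports that "30% of patients refuse treatment with CPAP due to several reasons including pressure effect of the mask" and cites 54% CPAP adherence at 3 months.

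**The concern.** T0 is an event after randomisation that some patients may never have. A control who never uses the device, or a TORS patient who is never operated on, gets no T0, and so no date on which the 6-month PG falls due. The analysis-set rule then removes the same patient. Each rule alone is enough to lose that patient from the primary comparison, so both need attention.

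The Introduction poses a pragmatic question about pooled conventional management and names refusal as a weakness of CPAP. If non-starters go unmeasured, the trial compares those who had TORS with those who took up a device. Randomisation does not protect that comparison, because starting is decided after allocation and for different reasons in each arm. For compliance, CPAP read-outs and treatment start dates exist only for patients who start. With no stated denominator, the reported figure may omit those who never began.

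A PG that was never scheduled cannot be recovered at the analysis stage, so a later analysis plan cannot repair this.

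**Working it through.** **1. The plan's own figure.** Section 2.8 gives 82% power with 21 per arm, a difference of 10.0, SDs of 10.0 and 12.0, and a two-sided alpha of 0.05. The standard error is √(10²/21 + 12²/21) = √11.62 = 3.41, and the noncentrality is 10/3.41 = 2.93 on 40 df. The noncentral t gives 81.7%. The stated power reproduces and is not in dispute.

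**2. Path of a randomised non-starter through the text.**
- Section 2.6: T0 needs surgery or a first day of device use. This patient has neither.
- Section 2.6: PG at 6 and 12 months and questionnaires at 3, 6 and 12 months are counted from T0, so none has a due date.
- Section 2.5: the primary endpoint is timed after the intervention, so it gives no other origin.
- Section 2.10: the patient had no intervention, so is outside the full analysis set. Correcting that rule alone would bring the patient back without an AHI value, and missing values are not replaced.
- A patient who starts and later stops has a T0 and is kept. Only non-initiation is lost.

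**3. Size in the control arm.** The share p who never start is not given. Assume 0 to 30%, the upper end being the Introduction's figure for CPAP refusal. Assume also that the 54% adherence applies to starters. Then controls with a T0 = 25 × (1 − p), and adherence among all allocated = 0.54 × (1 − p).

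| p | With T0 | Without T0 | Adherence, starters | Adherence, all allocated |
|---|---|---|---|---|
| 0% | 25 | 0 | 54% | 54% |
| 10% | 22.5 | 2.5 | 54% | 48.6% |
| 20% | 20 | 5 | 54% | 43.2% |
| 30% | 17.5 | 7.5 | 54% | 37.8% |

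**4. Direction for AHI.** Let p and q be the non-start shares in the control and TORS arms. Let D_C and D_T be the amounts by which non-starters' mean AHI exceeds starters' in each arm. The control-minus-TORS difference in all randomised patients equals the starters-only difference plus p·D_C − q·D_T. For illustration, set both D values to 10 (an assumption):
- p = 30%, q = 0: 3.0 − 0 = +3 points, so starters-only understates the benefit of TORS.
- p = 0, q = 30%: 0 − 3.0 = −3 points, so starters-only overstates it.
- p = q: no net shift.

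The design difference is 10. The article gives none of p, q, D_C or D_T.

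**5. Power.** With 17 or 18 controls against 25 TORS patients (p = 30%, no other loss), power is about 78 to 83%, depending on which arm has the SD of 12. Power is not the main cost. Selection is.

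**The case against.** **The visits are assigned by group.** Section 2.6 says that the CPAP or MAD group will be seen and will have PG, which can be read as everyone allocated. No section says that a non-starter is not seen, and a condensed article may leave visit detail to a fuller protocol. This stands in part: the loss is an inference. But the article itself states the time origin and the analysis set, and under those two rules a non-starter has neither a due date nor a place in the analysis.

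**Timing from treatment start is deliberate.** Section 2.5 explains that 6 months allows for postoperative recovery and for device use to settle. This stands, and is why T0 should be kept for patients who start in time.

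**Compliance is not confined to starters.** A reader might infer that compliance is counted only from first use and that refusal lies outside the objective. The article does not say so. It fixes no denominator, and recording start dates could itself reveal who never began. What remains is that the denominator is open and that no section plans to count non-starters.

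**The worst case is unlikely.** The 30% is a background figure for CPAP. One reason given is mask pressure, so some of those patients may have tried the device and would have a T0. Controls here choose CPAP or MAD with their physician, and they consented knowing that they might be allocated a device. The 38% further assumes that the 54% refers to starters; if the two rates overlap, it counts refusal twice. All of this stands, so the figures are a range and not a forecast.

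**Conclusion.** The point holds for the schedule and the analysis set together. As written, a patient in either arm who never starts has no date for the primary PG and is excluded from the analysis, which contradicts the stated intention-to-treat principle.

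The size is unknown: 0 to 7-8 of 25 controls for an assumed 0 to 30% never starting, and adherence among all allocated between 54% and 38% if the 54% applies to starters. The number of unoperated TORS patients cannot be estimated from the article.

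A reader might conclude that the rule flatters the device arm. The article does not support that. Losing untreated controls would favour the devices, losing unoperated TORS patients would favour TORS, and neither rate is given. For compliance the direction is clearer: if the denominator is starters only, the figure cannot be lower than the one for all allocated.

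**What to change.** **Section 2.6.** Keep T0 as written for patients who start by a prespecified date after randomisation. For any patient not started by then, set T0 to that date and keep it even if treatment begins later. Do the 3-, 6- and 12-month questionnaires and the 6- and 12-month PG on that clock.

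**Section 2.10.** Delete the exclusion for no study intervention, so that these measurements enter the primary analysis. Changing section 2.6 alone would obtain the PG and then discard it. State also that not starting is not in itself a major protocol violation, or the same patients could leave by that route.

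**Compliance.** Report it over all patients allocated to CPAP or MAD, counting never-starters as zero use. Report the interval from randomisation to T0 by arm.

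**Cost.** A few sentences, and follow-up of patients already within the 50. No treatment changes. Reported compliance becomes less favourable, time on treatment varies among late starters, and some non-starters will still decline PG. The change should be made before the first 6-month PG falls due.

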### Informed consent

2.7

Documented informed consent will be obtained for all patients included in the study before they are registered in the study. This will be done in accordance with the national and local regulatory requirements. The informed consent procedure will conform to the ICH guidelines on Good Clinical Practice. This implies that “the written informed consent form will be signed and personally dated by the patient or by the patient's legally acceptable representative”. Patients will be given sufficient time for consideration. An independent physician will be available accordance with the requirements of the national law. It is the responsibility of the investigator to obtain signed informed consent from every patient prior to the start of any study related procedure.

### Sample size calculation

2.8

To answer our primary objective 25 patients per arm must be included in the study. This sample size calculation is based on results of an earlier RCT where OSA surgery was compared to conventional therapy (medical management) [26]. At 6 months MacKay et al. found the means of AHI to be in group 1, the conventional group 34.5 with a standard deviation of 23.0 and in group 2, the surgery group 20.8 with a standard deviation of 18.4. We have chosen to select a smaller standard deviation compared to the literature, as retrospective analysis of our database of OSA patients treated with TORS show a mean of AHI at 3 months (n = 31) of 16.4 with a standard deviation of 12.0 and a mean of AHI at 1 year (n = 14) of 10.8 with a standard deviation of 8.48. As our inclusion and exclusion criteria are strict and like our retrospective data and we expect a similar outcome. Given the sample size, analyses will primarily focus on estimating treatment effects with 95% confidence intervals. Secondary outcomes and subgroup analyses will be considered exploratory. Group sample sizes of 21 and 21 achieve 82% power to detect a difference of 10.0 between the null hypothesis that both group means are 34.0 and the alternative hypothesis that the mean of group 2 is 24.0 with estimated group standard deviations of 10.0 and 12.0 and with a significance level (alpha) of 0.05 using a two-sided two-sample *t*-test. The detectable differences are estimated to be of clinical relevance. To correct for possible missing data, we calculated a 20% bigger sample size which results in a sample size of 25 patients per arm.

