### Study setting

2.1

This study is single-site, two-arm, parallel-group, randomized controlled trial, in a general hospital, the Frisius Medical Center located in Leeuwarden, the Netherlands. The trial aims to compare the clinical effectiveness of TORS versus non-surgical therapy (CPAP or MAD) in patients with moderate to severe OSA and will include 50 patients eligible for surgery randomized into either group 1 receiving TORS BOT reduction (*n* = 25) or group 2 CPAP or MAD (*n* = 25), depending on clinical preference. The duration of the trial is estimated to be approximately two years. The trial design is visualized in Fig. 1.

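### The 82% power in section 2.8 is computed correctly but rests on a control mean (34.0) and a control SD (10.0) that nothing in the article supports for a CPAP/MAD arm

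*Protocol article*

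**What the plan says.** All planning figures are in section 2.8 (Sample size calculation) of the protocol article.

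- **Cited trial.** An earlier randomised trial of surgery against medical management gave, at 6 months, a mean AHI of 34.5 (SD 23.0) with conventional treatment and 20.8 (SD 18.4) with surgery.
- **Local data.** TORS patients only: mean 16.4 (SD 12.0, n = 31) at 3 months and 10.8 (SD 8.48, n = 14) at 1 year.
- **Reason for a smaller SD.** "We have chosen to select a smaller standard deviation compared to the literature, as retrospective analysis of our database of OSA patients treated with TORS" gave those lower values. The section adds that the trial's criteria are strict and resemble those behind the retrospective data.
- **Power statement.** "Group sample sizes of 21 and 21 achieve 82% power to detect a difference of 10.0". The hypotheses are set out as "the null hypothesis that both group means are 34.0 and the alternative hypothesis that the mean of group 2 is 24.0". The assumed spread is "estimated group standard deviations of 10.0 and 12.0". The test is specified "with a significance level (alpha) of 0.05 using a two-sided two-sample" t-test.
- **Allowance for missing data.** "we calculated a 20% bigger sample size which results in a sample size of 25 patients per arm".

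Elsewhere, section 2.3 gives the control arm CPAP or MAD. The Introduction says "CPAP effectively reduces apnea hypopnea index (AHI), improves sleep quality" and credits MADs with an effective reduction as well. Section 2.1 has "group 1 receiving TORS BOT reduction", and section 2.9 numbers the arms the same way. In section 2.8, group 1 is the conventional arm.

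**The concern.** The two control inputs come from different kinds of patient. The mean sits beside that of a medical-management arm. The SD is less than half of that arm's, and the reduction is argued from patients who had surgery. The article gives no AHI mean or SD for any CPAP- or MAD-treated group, and the only control-arm SD it reports is 23.0.

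The 82% is stated without condition for the primary endpoint. A reader who meets a null result may take it as coming from a trial with a four-in-five chance of detecting 10/h. The same inputs fix the expected precision, and section 2.8 says the analysis will concentrate on estimates with 95% confidence intervals.

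**Working it through.** **Method.** Two-sided two-sample t-test, alpha 0.05, n per arm:

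- SE = √[(s₁² + s₂²)/n], df = 2n − 2, noncentrality = difference/SE
- power from the noncentral t distribution
- expected CI half-width ≈ t(0.975, df) × SE

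**1. The plan's own figure.** SDs 10.0 and 12.0, n = 21, difference 10: SE = √(244/21) = 3.41; noncentrality 2.93; df = 40; critical t = 2.021. Power is 81.7%, which matches 82%. Half-width 2.021 × 3.41 = 6.9. Exchanging the two SDs between arms changes nothing.

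**2. The control SD of the cited arm.** Difference kept at 10.

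- Control 23.0, TORS 12.0, n = 21: SE = √[(529 + 144)/21] = 5.66; noncentrality 1.77; power 40.7%; half-width 11.4.
- Control 23.0, TORS 18.4, n = 21: SE = √[(529 + 338.56)/21] = 6.43; noncentrality 1.56; power 33.0%; half-width 13.0.

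**3. Across control SDs.** The rows for 15 and 20 are illustrative values, not figures from the article.

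| Control SD | TORS SD | Power, n = 21 | Half-width, n = 21 | Power, n = 25 | Half-width, n = 25 |
|---|---|---|---|---|---|
| 10 | 12 | 82% | 6.9 | 88% | 6.3 |
| 12 | 12 | 75% | 7.5 | 82% | 6.8 |
| 15 | 12 | 64% | 8.5 | 72% | 7.7 |
| 20 | 12 | 48% | 10.3 | 56% | 9.4 |
| 23 | 12 | 41% | 11.4 | 47% | 10.4 |
| 23 | 18.4 | 33% | 13.0 | 38% | 11.8 |
| 23 | 8.48 | 45% | 10.8 | 52% | 9.9 |

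**4. Do the planned mean and SD belong together?** In the four groups reported in section 2.8, SD/mean is 23.0/34.5 = 0.67, 18.4/20.8 = 0.88, 12.0/16.4 = 0.73 and 8.48/10.8 = 0.79. The planned control arm has 10.0/34.0 = 0.29. Four groups do not make a rule, but no group in the article combines a mean near 34 with an SD near 10.

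**5. The control mean.** Power depends on the difference, not on 34.0 itself. The mean matters because the 10/h advantage presumes controls who stay near 34. With the planned SDs, 21 per arm and the planned TORS mean of 24.0, an assumed control mean of 30 leaves a difference of 6 and 40% power. A control mean of 26.4 leaves 2.4 and 11%. At 24 there is nothing to detect.

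**6. Missing data.** 21 × 1.2 = 25.2, stated as 25. A loss of 20% leaves 25 × 0.8 = 20 per arm, with power 79.7% even at SDs 10/12. Keeping 21 evaluable allows a loss of 1 − 21/25 = 16%.

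**The case against.** **The cited arm cannot be rejected for its mean and trusted for its SD.** This stands. If CPAP/MAD controls differ from medically managed patients, 23.0 is not known to be their SD. Because SD tends to follow the mean in the reported figures, a treated arm with a lower mean could well vary less. A reader might infer that true power is 33% to 47%. The article does not support that. Those figures apply only if the controls resemble the cited arm, and the range mixes 21 with 25 per arm. At the 21 to which the 82% refers, it is 33% to 41%.

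**Other figures in the article are kinder.** Also true. An SD of 12.0 in both arms gives 75% to 82%, though it borrows a surgical SD for the controls. The cited control arm (34.5, SD 23.0) against the local TORS result (16.4, SD 12.0) gives a difference of 18.1 and 88% power at 21 per arm. The cited trial's own difference, 34.5 − 20.8 = 13.7, gives 55% (SDs 23.0/18.4) to 66% (23.0/12.0). Planning for 10 is therefore a smaller target than either observed difference and is not a fault in itself. Both larger differences, however, still rest on a medically managed control mean.

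**The smaller SD is not argued from TORS data alone.** Correct: strict eligibility is also given as a reason, and the criteria apply to both arms. But the comparison offered is with a TORS database, so it says little about spread on CPAP or MAD.

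**The limits are acknowledged.** The Discussion admits the small sample and promises caution over non-significant findings. That lessens the harm. It does not qualify the 82%, and it speaks of modest differences and mainly of secondary outcomes.

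**Conclusion.** The concern holds as a fault of inputs, not of calculation. The 82% is right for SDs of 10.0 and 12.0 and a difference of 10/h, and the article supports neither the control SD (10.0, or 12.0 if the labels are reversed) nor the control mean for a CPAP/MAD arm. The two cannot be defended together:

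- If the controls are like the cited arm, 23.0 comes with the mean. Power at 21 per arm falls to about 41% or 33% (47% or 38% at 25), and the half-width at 21 per arm rises from 6.9 to 11.4–13.0.
- If the controls are effectively treated, the SD may be smaller, but the assumed 10/h advantage over a mean of 34 has no basis.

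These figures assume a difference of 10, a two-sided alpha of 0.05 and the t-test. That the mean was taken from the cited arm is an inference: 34.0 is close to 34.5, and section 2.8 says the calculation is based on that trial.

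Two side issues are minor. The group numbering in section 2.8 runs against sections 2.1 and 2.9, so under the trial's labels the stated alternative would favour the devices. A reader might infer that the planned direction is wrong, but section 2.8 defines its own labels when describing the cited trial, and two-sided power is the same either way. The inflation matches its wording, a sample 20% bigger; the article does not claim that 21 per arm survive a 20% loss.

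**What to change.** Keep n = 50 and revise section 2.8:

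1. State that 82% is conditional on SDs of 10 and 12 and a difference of 10/h with 21 evaluable per arm.
2. Base the control mean and SD on CPAP/MAD-treated patients, or label them as assumptions, and give the expected direction of the difference.
3. Add a short table of power and expected CI half-width for control SDs from about 10 to 23, at 21 and 25 per arm, and say that the true control SD is unknown.
4. Minor: use the group numbering of sections 2.1 and 2.9, and say that 25 per arm keeps 21 evaluable only up to 16% loss (20 per arm gives 79.7% on the plan's own SDs).

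The cost is rewording one section and a less favourable, conditional power statement. No patients are added, and the primary endpoint and test are unchanged.
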